**Figure 1 F1:**
[figure not shown]
Flowchart for inclusions, interventions, and assessments. ^1^SIAS, Social Interaction Anxiety Scale; ^2^MDI, Major Depression Inventory; ^3^SAD, Social Anxiety Disorder; ^4^GDPR, General Data Protection Regulation; ^5^PSE, Present State Examination.

### Inclusion criteria

Participants must meet the following inclusion criteria:

Age 18–75.Sufficient knowledge of the Danish Language.Fulfilling the diagnostic criteria for SAD according to ICD-10 classification of mental and behavioral disorders (F 40.1) (1).

### Exclusion criteria

Previously diagnosed with autism spectrum disorders.Previously diagnosed with psychotic disorders.Severe depression (>29 MDI).Dependence syndrome according to ICD-10 classification of mental and behavioral disorders (F1x.2) (1).Suicidal ideation.Dementia/Intellectual disability.Epilepsy.Taking part in other kinds of psychological intervention for SAD.Medication (SSRI, benzodiazepine, MAOI) type and doses needs to be stable three months prior to inclusions and during the intervention.

### Randomization and blinding

Participants are block randomized (1:1) using random block size. The block sizes will not be disclosed, to ensure concealment. Computer generated random numbers using the platform Sealed Envelope (https://www.sealedenvelope.com) will be used to generate the allocation sequence. The allocation sequence is handled by a data manager from the Patient data Explorative Network (OPEN) and is unavailable to those who enroll and assign participants. We will use the randomization module in REDCap (Research Electronic Data Capture) to assign participants. To prevent foreknowledge of treatment assignment to affect enrollment, the psychologist responsible for the diagnostic interview is blind to treatment assignment. Participants are blinded to their treatment assignment until their first treatment session. Participants will only be blind to treatment assignment at the pre-test but not at later assessments. A clinician blind to treatment assignment will administer the assessment taking place at pre-test, mid-test, and post-test.

### Sample size

A recent study reported ~10-point drop in SIAS for standard treatment and 20-point drop for traditional VR-exposure with standard deviations around 15 points (22). With adaptive/tailored VR-exposure we find it reasonable to assume a similar effect size (d = 0.66 and 1.33, respectively). The standard variation is between participants, which we expect to be conservative for our paired design. Using the measurement error based on test-retest reliability of the SIAS a drop of 13 points is considered a statistical reliable change (41). Meta-analyses have indicated smaller effect sizes, but the analyses are still based on rather few RCTs, which did not benefit from the improvements we propose in this study. If 35 participants are recruited for each group, this will lead to a statistical power of 0.80 comparing the VR-treatment to in vivo-treatment at the 0.05 significance level. To consider a 20% dropout we plan to invite 90 participants in total.

### Interventions

Interventions are carried out by psychologists with at least one full year of clinical experience. Before the study therapists are trained delivering treatment in accordance with the treatment manual. The manual is reviewed with the principal investigator and the different sessions of the intervention is practiced through role-play. Therapy sessions will take place at the Center for Digital Psychiatry with one therapy room for VR-treatment and one for *In vivo*-treatment.

#### VR-treatment

The intervention is an individual manual-based cognitive behavioral therapy with adaptive exposure in VR. The intervention consists of a 10-week treatment program with 1 h weekly session adapted from Clark and Wells (13, 42). The treatment rationale is based on a model of the maintenance of social phobia developed by Clark and Wells, and the treatment aimed at reversing the maintaining processes identified by the model (13). Sessions dedicated to exposure are scheduled from the fourth to the ninth session. The three first sessions are dedicated to building the therapeutic relationship and providing psychoeducation in addition to providing a rationale for exposure therapy. The themes of therapy are: (a) The general ideas of CBT, (b) The maintaining processes of social phobia, (c) negative automatic thoughts, (d) shifting focus of attention form self-focus to external focus, (e) safety behaviors, (f) post-processing, (g) self-processing, (h) schemas and rules for living. The last session is dedicated to evaluation and relapse prevention. In session and for homework assignments worksheets are used extensively to practice and reinforce the skills learned in therapy. The intervention utilizes homework assignments including *in vivo* exposure.

##### Exposure in VR

We will use 360° videos for exposure using an HTC VIVE Pro headset. The HTC VIVE Pro has a field of view of 110°, the resolution per eye is 1,440 × 1,600 pixels with a refresh rate of 90 Hz. It has 6 DoF tracking capabilities, however 360° videos only allow for experiencing 3 DoF. The 360° videos we will use for exposure was recorded using Insta360-InstaOneX and edited using the game engine Unity 3D.

Six different VR-scenarios will be used for exposure: (1) Taking a seat on a bench in a public park, (2) Being introduced as a new employee, (3) Performing a presentation at a meeting, (4) Entering and shopping in a grocery store, (5) Visiting a café, and (6) Using public transportation. VR exposure for SAD has so far predominately been conducted using computer-generated virtual environments (21–23). However, at least three studies conducted used 360° videos in the treatment of SAD (43–45). A feasibility study from our lab showed that 360° videos are able to trigger anxiety in individuals with SAD (46).

The scenarios were chosen in order to reflect different situational domains of social anxiety including informal speech/interaction, formal speech/interaction, observation by others and assertion (47). All scenarios consist of multiple scenes with both participant and therapist choices. The therapist can choose the length of the exposure as well as the difficulty of the exposure.

Participants will be seated during all exposures in VR and will interact with the environment through integrated eye-gaze options, most commonly utilized for movement (e.g., sitting down, entering a room) as well as indicating choices (e.g., “ask the shop assistant” or “await the shop assistant”). Other interaction options include dialogue, where the clinician controls scene changes and reactions from the environment, prompting a second question from the boss when the participant, as a new employee, is finishing answering the first one.

While the participant is in the VR-scenario, data on HR and EDA are collected using iMotions software. These data are collected to continuously estimate the anxiety experienced by the participant. The therapist can watch the VR-scenario on a monitor, while the participants are in VR. On the monitor, the participant's anxiety level will be displayed (low, medium and high), and act as a guide to aid the therapist decisions on how to conduct the exposure (i.e., the length and the intensity of the exposure). Continuous estimates of the participants anxiety level allows for frequent assessment without disturbing the participants' sense of presence in VR. Data on the participant's anxiety levels during exposure along with recorded video is available after the exposure and can be included as a tool in the therapy session.

The exposure treatment is personalized to each participant. The therapist and participant can choose which scenarios they find most useful in achieving treatment goals. It is allowed to use the same VR-scenarios for two or more exposure sessions.

#### In vivo-treatment

The intervention is an individual manual-based cognitive behavioral therapy. The intervention consists of a 10-week treatment program with 1 weekly session adapted from Clark and Wells (13, 42). Sessions dedicated to exposure *in vivo* are scheduled from the fourth to the ninth session. Exposure will take place at the Center for Digital Psychiatry and the surrounding areas. The therapist will plan the exposure with the participant and will accompany the participant during the exposure. Themes of the therapy are similar to the VR-treatment. *In vivo* exposure is also conducted as homework. The amount and intensity of the exposure during session and assigned as homework are matched between the two interventions. *In vivo* exposure is personalized based on treatment goals. The level of intensity of the exposure is based on the participants anxiety hierarchy.

#### Criteria for discontinuing allocated intervention

If participants fail to meet for an appointment, they will receive a letter to remind them of the agreed treatment plan. Participants, who fail to meet for appointments for treatment more than three times in total will be excluded from treatment.

#### Treatment fidelity

The interventions are manualized to increase treatment fidelity. To ensure that the treatment is delivered consistently and reliably in accordance with the manual the therapist will after each treatment session answer a self-report questionnaire on specific treatment targets for each session (48).

### Data collection and management

Data in relation to the primary and secondary outcomes will be collected at pre-treatment (week 1), mid-treatment (week 5), post-treatment (week 10) and at 6 months follow-up (week 36) and 12 months follow-up (week 62). Figure 2 provides an overview of the planned assessments. Data collected from the participants using self-report measures and data reported by therapist are collected using REDCap. REDCap is an electronic data capture tool and is hosted by OPEN, which is part of the REDCap Consortium. To ensure confidentiality assigned researchers and the data manager at OPEN will be the only people with access to data at REDCap. Informed consent forms will be scanned and stored in REDCap. Data is stored at OPEN's server located in the Regions of Southern Denmark. SUDS, HR, EDA, and estimated anxiety is collected using iMotions, and data is saved on a secure folder on SharePoint. Both REDCap and SharePoint complies with the Danish Data Protection Act and the General Data Protection Regulation (GDPR). Data from REDCap will be exported to statistical software (SPSS, Stata, and R) on OPEN's server located in the Region of Southern Denmark. Personal identifiers in the dataset have been flagged and will not be exported from REDCap to ensure confidentiality.

**Figure 2 F2:**
[figure not shown]
Schedule of enrollment, interventions, and assessments. ^1^SIAS, Social Interaction Anxiety Scale; ^2^ LSAS-SR, Leibowitz Anxiety Scale-Self report version; ^3^FNE-B, Fear of Negative Evaluation-Brief version; ^4^MDI, Major Depression Inventory; ^5^AUDIT, Alcohol Use Disorders Identification Test; ^6^DUDIT, Drug Use Disorders Identification Test; ^7^WAI, Working Alliance Inventory; ^8^SUDS, Subjective Units of Distress Scale; ^9^SSQ, Simulator Sickness Questionnaire; ^10^SWEAT, Specific Work for Exposure Applied in Therapy.

### Availability of data and materials

[name] will have access to the full trial dataset. Data will be stored on OPEN's server located in the Region of Southern Denmark. February 2025 data will be transferred to The Danish National Archives. Data are available upon reasonable request. Restrictions apply to the availability of data and approval is needed from Danish Data Protection Agency and or The Danish National Archives.

### Assessment

#### Primary outcome measure

SIAS measured at pre-treatment, mid-treatment, post-treatment and at follow-up (6 and 12 months). The instrument is a measure of social anxiety symptoms and consists of 20 items assessing cognitive, affective, and behavioral responses to social interaction. In a comparison of social phobia outcome measures Cox et al. found strong support for SIAS which showed good sensitivity to treatment effects (49). The scale ranges from 0 to 80. Participants have to indicate to what degree they feel each statement is characteristic to them using a 5-point Likert scale (0 = not at all, 1 = slightly, 2 = moderately, 3 = very, 4 = extremely). The instrument has high internal consistency, Cronbach's alpha = 0.93, and high test-retest reliability, r = 0.92 (50).

#### Secondary outcome measures

Leibowitz Anxiety Scale-Self-report version (LSAS-SR) measured at pre-treatment, mid-treatment, post- treatment and at follow-up. LSAS-SR is a measure of anxiety and avoidance in a range of social situations (51).

Fear of Negative Evaluation-Brief version (FNE-B) measured at pre-treatment, mid-treatment, post-treatment and at follow-up. FNE-B is a measure of distress experiences when getting negative evaluations by others (52).

Major Depression inventory (MDI) measured at pre-treatment, post-treatment and at follow-up. MDI is a measure of symptoms severity in depression (53).

EQ-5D-5L measured at pre-treatment, mid-treatment, post-treatment and at follow-up. EQ-5D-5L is a measure of health status (54).

#### Other measures

Alcohol Use Disorders Identification Test (AUDIT) measured at pre-test. AUDIT is a screening for unhealthy alcohol use (55).

Drug use disorders identification test (DUDIT) measured at pre-test DUDIT is a screening instrument for drug-related problems (56).

Specific Work for Exposure Applied in Therapy (SWEAT) measured after each exposure session (session 3 to 9). SWEAT is answered by the therapist and measures costs and efforts required to conduct exposure (57).

Working Alliance Inventory (WAI) measured post-treatment. WAI measures the collaborative engagement of therapist and participant (58).

Subjective Units of Distress Scale (SUDS) will be measured during exposure in virtual reality at session 3 to 9. SUDS is used to measure intensity of anxiety experienced by the participant during exposure (59).

Heart rate (HR) is collected using an optical heart rate sensor (Polar Verity Sense). The heart rate sensor provides the heart rate in 1-s interval based on a sampling rate of 135 Hz. Data is collected using the iMotions software. HR will be collected during exposure in VR.

Simulator Sickness Questionnaire (SSQ) measured after each exposure session in VR. SSQ is answered by the participant after each exposure session in VR and it is a measure of simulator sickness (60).

Electrodermal Activity (EDA) is collected using BioPAC systems. Data is collected at a sampling rate of 1,000 Hz. Data is collected using the iMotions software. EDA will be collected during exposure in VR.

Estimated Anxiety is collected using iMotions software. The estimation of anxiety is based on HR and EDA measurements utilizing artificial neural networks (NeuroEvolution of Augmenting Topologies). Estimated anxiety (low 0–33 on SUDS, medium 34–66 SUDS, high 66–100 on SUDS) will be collected during exposure in VR.

### Statistical analyses

The primary statistical analysis will be carried out as intention to treat (ITT). We will use linear mixed models to analyze the data. Separate analysis will be performed for each outcome variable. A two-level model with observations nested within participants is used. The fixed effects will be time, intervention, and the interaction between time and intervention as well as the baseline score. In addition to the primary analysis, a per-protocol analysis will be carried out on those participants completing at least 50% of the exposure sessions, interpreting the results cautiously due to the potential selection bias and confounding. Linear mixed models produce accurate estimates under the assumption that data are missing at random (MAR). A sensitivity analysis will be carried out where missing data will be handled by multiple imputation (m=100). Imputations will be based on baseline characteristics and secondary outcomes used chained equations. The moderating effect of the working alliance, depressive symptoms, alcohol, and drug use on the treatment outcome will be explored as subgroup analysis with continuous moderators by including them as covariates interacting with treatment and time. Model validation in the linear mixed model will be performed by inspection of qq-plots of residuals and best linear unbiased predictors to assess normality, and plotting residuals against fitted values to check homoscedasticity. If assumptions are violated, analysis will be performed after log-transformation. If assumptions do not hold under log-scale, bootstrapping will be applied with the linear mixed model, taking bootstrap sampling clustered by participant, and estimating post-treatment effect using bias-corrected accelerated confidence intervals (61).

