#### Secondary hypotheses

At 6 and 12 months follow-up, we expect that VR-treatment will result in lower levels of social anxiety than *in vivo*-treatment.Post treatment and at 6 and 12 months follow up we expect that VR-treatment will result in lower levels of depression and higher levels of self-rated health than *in vivo*-treatment.The dropout rate we expect will be lower for the VR-treatment compared to the *in vivo*-treatment.

In addition to the evaluation of effect, a health economic evaluation will be made from a societal perspective.

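### As worded, the multiple-imputation sensitivity analysis does not name treatment arm as a predictor; followed literally it would shrink the SIAS difference, and it cannot show robustness to departures from MAR

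*Protocol article*

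**What the plan says.** All of this is in the protocol article. Under Statistical analyses, the primary intention-to-treat analysis is a linear mixed model: "The fixed effects will be time, intervention, and the interaction between time and intervention as well as the baseline score". The missing-data basis is given as "Linear mixed models produce accurate estimates under the assumption that data are missing at random (MAR"). The next sentence reads "A sensitivity analysis will be carried out where missing data will be handled by multiple imputation (m=100"), followed by the predictors: "Imputations will be based on baseline characteristics and secondary outcomes used chained equations". No other missing-data analysis is described.

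Under Primary outcome measure: "SIAS measured at pre-treatment, mid-treatment, post-treatment and at follow-up (6 and 12 months"). Under Secondary outcome measures the scales are LSAS-SR, FNE-B, MDI and EQ-5D-5L, for example "Leibowitz Anxiety Scale-Self-report version (LSAS-SR) measured at pre-treatment, mid-treatment, post- treatment and at follow-up". SIAS is the primary outcome, so its post-baseline scores are not in that group.

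Under Secondary hypotheses, dropout is expected to differ by arm: "The dropout rate we expect will be lower for the VR-treatment".

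**The concern.** An imputation model should contain at least the terms of the analysis model it feeds. Here the analysis estimates an arm effect at each time, while the stated predictors include neither arm nor SIAS at mid-treatment or follow-up. If arm is left out, dropouts in both arms with the same predictor values are imputed from one common distribution, and the imputed part of the sample carries the arm effect only as far as the predictors carry it. The sensitivity estimate would then be smaller than the primary one because of its own specification, and could be misread as fragility of the primary result.

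Separately, imputation without a shift or reference-based step rests on MAR, as the mixed model does. Agreement between the two would not show how the result behaves if dropouts did worse than their observed data predict. That matters here because the endpoint is self-rated, participants know their treatment after the pre-test, and 20% dropout is planned for.

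**Working it through.** **1. The plan's own figures.** The Sample size section assumes a "10-point drop in SIAS for standard treatment and 20-point drop for traditional VR-exposure with standard deviations around 15 points". The difference is 20 − 10 = 10 and d = 10/15 = 0.67. For a two-sided 0.05 test with power 0.80, n per arm = 2 × (1.96 + 0.84)² × 15²/10² = 35.3, rounded up to 36; 35 per arm gives power 0.796. Allowing for 20% dropout, 70/0.80 = 87.5, so 88, against 90 planned. The figures reproduce within rounding, and 10 points, SD 15, N = 90 and 20% missing are used below.

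**2. The two models side by side.** Analysis model: time, intervention, time × intervention, baseline score. Named imputation predictors: baseline variables and the four secondary scales. Baseline SIAS plausibly falls in the first group. Arm falls in neither, and nor does post-baseline SIAS.

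**3. Ceiling by hand.** Let a fraction p be missing in each arm, and let the predictors carry no information on arm. Imputed values then have the same mean in both arms, so the completed-data difference is about (1 − p) × 10. For p = 0.20 this is 8.0, a loss of 2.0. The loss falls as the predictors carry more of the arm effect.

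**4. Simulation.** There were 1,500 trials per setting, with a true effect of −10. Post-treatment SIAS was imputed by proper Bayesian linear regression and then analysed by ANCOVA on baseline. Assumptions not in the documents: correlation 0.6 between visits and between scales; half the effect present at mid-treatment; missingness depending on mid-treatment SIAS; one secondary scale; 20 imputations. ANCOVA stands in for the mixed model. Monte Carlo error per entry is about 15 × √(1 − 0.6²) × √(4/90)/√1500 = 0.07, and entries in one row use the same simulated trials.

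| Missing | Post-treatment secondary scale in dropouts | Arm and SIAS included | List as worded, no arm | Loss |
|---|---|---|---|---|
| 20% | observed, same standardised effect | −10.06 | −9.34 | 0.72 |
| 20% | observed, half the effect | −9.87 | −8.50 | 1.37 |
| 20% | missing with SIAS | −10.00 | −8.23 | 1.77 |
| 20% | observed, no effect | −10.09 | −7.99 | 2.10 |
| 10% | observed, same effect | −10.00 | −9.64 | 0.36 |
| 10% | missing with SIAS | −10.01 | −9.11 | 0.90 |
| 30% | observed, same effect | −10.09 | −8.97 | 1.12 |
| 30% | missing with SIAS | −9.96 | −7.33 | 2.63 |

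A second simulation with baseline-to-post correlation 0.5 and 300 replicates gave, at 20% missing, 9.0 with the secondary scale observed, 7.9 with it missing, and 9.8 to 10.1 with arm included.

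**5. Which omission causes the loss.** At 20% missing with the secondary scale also missing, keeping arm but dropping mid-treatment SIAS gave −9.99, against −10.00 with both. Keeping mid-treatment SIAS but dropping arm gave −8.41. Across the four 20% settings, that second variant lost 0.56, 1.06, 1.59 and 1.57 points in table order. The bias comes from omitting arm.

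**6. Departure from MAR.** If only VR-arm dropouts were δ points worse than MAR predicts, the effect would be 10 − 0.20 × δ: 9.0 for δ = 5, 8.0 for δ = 10, and 7.4 for δ = 13 (the Sample size section's reliable-change figure). Imputation under MAR cannot display this, whatever its predictors.

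**The case against.** The strongest reply is that this is one sentence in a condensed article. It does not say that only these predictors are used. It can be read as naming what is added to the analysis-model variables, and a full analysis plan may specify imputation by arm. That stands: a reader might infer that the imputation certainly omits arm and is biased, and the article does not establish it. The loss is conditional on a literal reading. Even so, the article chose to give method, number of imputations and predictors, and arm is not among them.

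Chained equations normally use the other incomplete variables, so SIAS at other visits would probably enter. That also stands, but step 5 shows it does not cure the omission of arm. Equally, a reader might blame the bias on leaving out SIAS. With arm kept there is essentially none; the cost is mainly precision and the plausibility of MAR.

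A reader might also infer that the imputation is offered as a test of MAR and fails at it. The text follows the MAR sentence but never states that purpose. Conditioning on scales that the separate mixed models do not use is a recognised sensitivity analysis in its own right.

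Nor does expected differential dropout show that MAR fails: dropout that depends on arm is compatible with MAR when arm is in the model. If dropout were 10% in VR and 30% in vivo, and dropouts in both arms were 10 points worse than predicted, MAR would understate the VR benefit by 10 × (0.30 − 0.10) = 2 points, a conservative error. The section on discontinuing allocated intervention also removes participants from treatment, not from assessment, so 20% dropout need not mean 20% missing SIAS.

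**Conclusion.** The point holds as a conditional one. Followed as worded, the imputation would pull a true 10-point difference toward zero by about 0.7 to 2.1 points at 20% missing, given the assumed correlations of 0.6. The low end needs post-treatment secondary scales that are observed in dropouts and respond to treatment as SIAS does. With those scales missing at the same visit the loss is about 1.8, and the high end arises when they are observed but show no arm effect. The loss is bounded by roughly the missing fraction. The scales are collected at the same assessments, so joint missingness is realistic, but the documents do not state it.

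The imputation also shares the mixed model's MAR assumption. It may make MAR more plausible, but it cannot show robustness to departures from it.

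A reader might infer that the trial's main result is at risk. It is not: the primary mixed model contains arm and is unaffected, and no stated decision rule rests on the imputation. This is a cheap improvement to the sensitivity analysis.

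**What to change.** Reword the imputation sentence to say that imputation is done separately by arm, or with arm and arm-by-time in the model, using SIAS at all visits together with the secondary outcomes and baseline variables. If imputing by arm proves unstable with so many scales and about 36 observed participants per arm (90 × 0.80/2), use the second form; with one variable per visit, arm as a predictor in every equation already lets its effect differ by visit. Describe the result as a MAR analysis.

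Then add a delta-adjusted version of the same imputation: add, for example, 5, 10 and 13 SIAS points to the imputed values, vary the shift by arm, and report the shift at which the conclusion changes.

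The cost is a couple of sentences, a few lines of code and one more sensitivity table. Data collection, the primary model and the 100 imputations stay as they are. If the full plan already includes arm, one clause saying so settles the first part.

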**Methods:**

The trial is a randomized controlled, assessor-blinded, parallel-group superiority trail. The study has two arms: (1) CBT including exposure *in vivo* (CBT-Exp), (2) CBT including exposure therapy using individually tailored VR-content and a system to track anxiety levels (CBT-ExpVR). Treatment is individual, manual-based and consists of 10 weekly sessions with a duration of 60 min. The study includes 90 participants diagnosed with SAD. Assessments are carried out pre-treatment, mid-treatment and at follow-up (6 and 12 months). The primary outcome is the mean score on the Social Interaction Anxiety Scale (SIAS) with the primary endpoint being post-treatment.

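### Working alliance is listed as a treatment moderator but is measured only post-treatment, so its interaction with treatment is open to bias and cannot be read as moderation

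*Protocol article*

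**What the plan says.** The Statistical analyses section plans that "The moderating effect of the working alliance, depressive symptoms, alcohol, and drug use on the treatment outcome will be explored as subgroup analysis", and specifies the model: "with continuous moderators by including them as covariates interacting with treatment and time". So four variables are given the same role.

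Their timing differs:

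- Alliance (Other measures): "Working Alliance Inventory (WAI) measured post-treatment". No other time point is given in the text. The same entry says that "WAI measures the collaborative engagement of therapist and participant".
- Alcohol (Other measures): "Alcohol Use Disorders Identification Test (AUDIT) measured at pre-test".
- Drug use (Other measures): "Drug use disorders identification test (DUDIT) measured at pre-test".
- Depression (Secondary outcome measures): "Major Depression inventory (MDI) measured at pre-treatment, post-treatment and at follow-up".

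The abstract describes the primary outcome as SIAS "with the primary endpoint being post-treatment". Data collection and management places the outcome assessments at weeks 1, 5, 10, 36 and 62, with week 10 as post-treatment.

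**The concern.** A moderator analysis asks whether the treatment effect differs between kinds of participant. The kinds must be defined by something that treatment cannot have changed. Alcohol use, drug use and depression each have a pre-treatment value. Alliance has none, because it forms during the allocated therapy and is recorded once, at the end.

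Three consequences follow.

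1. **Arm and improvement can both shape the score.** The therapist accompanies the participant in one arm and runs the scenario from a monitor in the other. By then participants know their arm and how much better they feel. A treatment-by-alliance term can therefore mix moderation, mediation and reverse causation.
2. **Time order.** Interacting alliance with time in the repeated-measures model uses a week-10 score to explain week-5 SIAS.
3. **Selection.** Participants who leave before post-treatment may have no alliance score. The protocol allows for 20% dropout and hypothesises lower dropout in the VR arm, so those with a score may be a post-randomisation subset that differs between arms.

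At stake is a published statement that VR exposure works better, or worse, when the alliance is good, which this design cannot support.

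**Working it through.** **The plan's own figures.** The plan gives no figure for the moderator analysis. The sample-size inputs used below do reproduce. A 10-point difference (20 minus 10) with SD 15 gives 10/15 = 0.667 SD. With 35 per arm and two-sided 5%, power is 0.796 by the normal approximation and 0.785 by the exact t-test, against 0.80 stated. Allowing for 20% dropout, 70/0.8 = 87.5, so 88, against 90 stated. Completers: 90 × 0.8 = 72.

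**Assumptions.** The documents give no alliance-outcome slope, no arm difference in slope and no alliance variance. All slopes below are assumed.

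**Model with no true moderation (n = 72, SD units).**

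- SIAS: y = 0.5 × baseline − 0.667 × arm + e, with e of SD 1
- Alliance: w = −s × y + noise of SD 1, where s may differ by arm
- Fit: y on arm, baseline, w and arm × w, by ordinary least squares

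Given baseline, the slope of y on w within an arm is −s/(1 + s²). The spurious interaction is about the difference between arms in that quantity. It is zero when s is the same in both arms.

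| s (VR vs in vivo) | s/(1+s²), each arm | Difference | False-positive rate |
|---|---|---|---|
| 0 vs 0 | 0 and 0 | 0 | about 5% |
| 0.5 vs 0.5 | 0.400 and 0.400 | 0 | about 5% |
| 0.3 vs 0.2 | 0.275 and 0.192 | 0.083 | 6 to 7% |
| 0.6 vs 0.2 | 0.441 and 0.192 | 0.249 | about 20% |
| 0.6 vs 0 | 0.441 and 0 | 0.441 | about 52% |

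The rates come from simulation with thousands of replicates per row. Reversing the arms in the 0.6 vs 0.2 row again gives about 20%.

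**Second set-up, in SIAS points.** Here improvement is regressed on arm, w and arm × w, with no baseline term. The true effect is 10 points, SD 15, and s is in SD of alliance per 15 points.

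- s = 0.6 vs 0.2: spurious interaction 15 × (0.441 − 0.192) = 3.7 points per unit of w. False-positive rate 27% at N = 90 and 23% at N = 70.
- s = 0.5 vs 0: 15 × 0.400 = 6.0 points; 53% and 42%.
- s = 0.5 in both arms, but outcome SD 18 vs 12: 10.8/1.36 − 4.8/1.16 = 7.9 − 4.1 = 3.8 points; 31% at N = 90. Equal slopes therefore protect only if the outcome variances are also equal.
- s = 0.5 in both arms, equal SD: interaction 0 and false-positive rate 5%. The arm coefficient adjusted for alliance is 10/(1 + 0.25) = 8.0 instead of 10.

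**The case against.** **The interaction need not be biased.** A reader might infer that the estimate is always biased. The calculation does not support that: with equal slopes and equal variances the false-positive rate is nominal, and with modest slope differences it is nearly so. The large rates need large assumed differences between arms. This objection stands. What it leaves is that the data would not show which case applies, so even an undistorted estimate could not be identified as moderation.

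**The simulated model is simpler than the planned one.** The plan is a two-level mixed model with repeated observations. The rates above come from a single time point and do not transfer directly. They show direction and rough range only.

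**The trial's treatment effect is not distorted.** The drop from 10 to 8.0 points might be taken as a loss in the main result. It is not: the primary model contains time, intervention, their interaction and the baseline score, and alliance is not in it. Nothing in the article says that the arm coefficient from a moderator model will be reported as the treatment effect.

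**The analysis is minor.** It is exploratory, no stated hypothesis concerns alliance, and the questionnaire is listed under other measures. This also stands and limits the weight of the point.

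**It could be left to a fuller document.** Which MDI value is used could be; a pre-treatment value exists, so that is no fault. Alliance is different, because the article fixes both its role and its single time point, and no analysis plan can supply a pre-treatment score. Figure 2 was not available here, but the text on timing is plain.

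**Conclusion.** The point holds in limited form. The interaction of post-treatment alliance with treatment is open to bias and cannot be interpreted as moderation. That conclusion rests on the stated timing and on what the questionnaire measures, and does not depend on the simulation.

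The size is not known from the documents. Under the assumed slopes, the false-positive rate at n = 72 runs from nominal to about 52%. Effects of arm on alliance, and missing alliance scores in those who leave, are plausible but not documented.

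The primary SIAS comparison, the sample size and the other three moderators are unaffected.

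**What to change.** In Statistical analyses, remove working alliance from the moderator list and state that the moderators are the pre-treatment MDI, AUDIT and DUDIT. Report post-treatment alliance by arm, or as an exploratory process or association analysis. Attach to it the caution about selection and confounding that the section already gives for the per-protocol analysis.

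This changes about one sentence and needs no new data. The cost is that the trial makes no moderation statement about alliance.

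An earlier alliance measurement is not needed for this fix. It would add an assessment, which may have to be communicated to the ethics committees as a protocol modification. It would also still be post-randomisation, so it could support a process analysis but not a baseline moderator.
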